## Abstract

**Background:**

The Communities That Care (CTC) prevention planning and implementation system trains communities throughout a five-phase cycle to (1) build capacity for prevention, (2) adopt science-based prevention, (3) assess the prevention needs of adolescents living in the community, (4) select, and (5) implement evidence-based programs according to their needs. After CTC proved to be effective and cost-effective in the U.S., it is being used by an increasing number of communities in Germany. The aim of this study is to evaluate the effectiveness and cost-effectiveness of CTC in Germany.

**Methods:**

Communities in CTC-phases 1 to 3 (*n* = 21) and individually-matched comparison communities (*n* = 21) were recruited for a non-randomised trial. To assess long-term outcomes, (1) a cohort of 5th Grade students will be surveyed biennially concerning behaviours (antisocial behaviour and substance use) and well-being as well as risk and protective factors. Additionally, (2) biennial cross-sectional surveys will be conducted in 6th, 8th, 10th, and 11th Grade in each community. To assess short-term outcomes, a cohort of ten key informants per community will be surveyed biennially concerning adoption of science-based prevention, collaboration, community support and community norms. (4) In a cross-sectional design, all ongoing prevention programs and activities in the communities will be assessed biennially and data will be collected about costs, implementation and other characteristics of the programs and activities. (5) To monitor the CTC implementation, the members of the local CTC-boards will be surveyed annually (cross-sectional design) about team functioning and coalition capacity. Data analysis will include general and generalised mixed models to assess the average treatment effect of CTC. Mediation analyses will be performed to test the logical model, e.g., adoption of science-based prevention as a mediator for the effectiveness of the CTC approach.

**Discussion:**

This is the first controlled study to evaluate the effectiveness of a comprehensive community prevention approach in Germany. Evaluating the effectiveness of CTC in Germany is an important prerequisite for further diffusion of the CTC approach.

**Trial registration:**

This study was registered with German Clinical Trial Register: DRKS00022819 on Aug 18, 2021.

## Background

Children and adolescent problem behaviour, such as antisocial behaviour, alcohol use, illicit drug use and delinquency, place a burden on healthy development and well-being [1–3]. Preventive programs aim to minimize these risk factors, strengthen corresponding protective factors, and promote resilience, which will be developed in a process of interaction between the individual and the environment [4–8]. In this context communities take a central function [9, 10]. They have the opportunity to shape this in a targeted manner via various institutions and settings as well as the establishment of intersectoral collaborations. But communities often have a lack of knowledge regarding prevention and health promotion, so that in many cases prevention programs and strategies are selected and implemented that show no or only limited effectiveness [11, 12] or have not yet been evaluated. Lack of program fidelity is also a problem [13, 14].

Building community networks for prevention strengthens the implementation and coordination of prevention programs [15–17]. So far, there are only a few studies that have investigated their effect on the health of the target group and can show effects [18–20]. A program used worldwide to build such community networks for prevention is Communities That Care (CTC).

CTC was developed in the U.S. in the 1980s. It supports communities in establishing healthy environments that enable children and adolescents to grow up safely and healthy. The Community Youth Development Study (CYDS) showed that CTC increased the adoption of a science-based approach to prevention, sectorial collaboration for prevention, and community support for prevention [21] as well as the number of implemented evidence-based prevention programs and the number of program participants in the community [22]. This resulted in lower incidences in smoking cigarettes, smokeless tobacco use, alcohol use and delinquent behaviour (Odds Ratios 1.41 to 2.34) compared to control communities [23]. The effects of CTC on youth problem behaviours were fully mediated by community adoption of a science-based approach to prevention [24]. Economic evaluations indicated that CTC may produce a return on investment of approximately US$10.23 for every dollar spent [25].

According to the CTC-model of community change it takes 1 year to observe improvements in throughputs, 2 years to observe effects in short-term outcomes and outputs, 3 years to observe mid-term outcomes and 5 years to observe long-term outcomes (Fig. 1). CTC’s theory of change and results from Brown et al. [24] suggest that the community adoption of a science-based approach to prevention is the primary mechanism of CTC.

**Fig. 1 Fig1:**
[figure not shown]
Communities That Care model of community change [cf. 6]

In 2009, CTC was transferred to Germany and has since been implemented in 33 communities. In this context, the database “Grüne Liste Prävention” (www.gruene-liste-praevention.de) has been developed, which includes German-language evidence-based prevention programs. A feasibility study in Lower Saxony showed the transferability (i.e., high level of acceptance and identification with the CTC approach in the model communities) of CTC to the German context [26, 27], but an evaluation of its effectiveness has not been conducted in Germany to date. The aim of this study is to evaluate the effectiveness and cost-effectiveness of CTC in Germany.

## Methods and design

### Intervention

#### Intervention condition

CTC implementation is organised into five phases [28]. Training in the various phases of the CTC process is provided by the CTC Training and Support Center (German Prevention Congress) to encourage communities to achieve milestones and benchmarks. Specially developed instruments support quality assurance and development. Figure 2 shows the objectives, activities, training and instruments for quality assurance in the respective phases.

**Fig. 2 Fig2:**
[figure not shown]
Overview of phases and components of the intervention [cf. 6]

#### Comparison condition

For the comparison communities, it was not examined whether they use an elaborated system of community prevention. Due to the international push of intersectoral community-based prevention approaches [29] through the WHO Ottawa Charter on Health Promotion [30] it can be assumed that the majority of these communities work with a local intersectoral network for prevention and health promotion. Böhm and Gehne [31] give an overview of such networks in Germany.

### Design

A quasi-experimental study will be conducted in small towns, rural communities and districts of major cities in four German federal states (Baden-Württemberg, Bavaria, Lower Saxony, Rhineland-Palatinate) to evaluate the effectiveness of CTC in Germany; hereinafter referred to as communities. The study is designed as a cluster non-randomised controlled trial [32]. To evaluate the effectiveness of CTC, data will be collected in a trend (repeated cross-sectional) and cohort design (Fig. 3). Additionally, the implementation of CTC will be evaluated (process evaluation). Funding provided, a follow-up will be conducted in 2025 and further years.

**Fig. 3 Fig3:**
[figure not shown]
CTC-EFF Study design and measures

### Assignment method and eligibility

The unit of assignment is the community, the assignment method is self-selection. Individual 1:1-matching (see below) was employed to help minimize potential bias induced due to non-randomization.

Sampling was initiated in April 2020 by inviting all German CTC-communities that would be in Phases 1 to 3 in the CTC cycle by January 2021. To be included in the trial, communities had to have at least one secondary school and willingness to sign a cooperative agreement for study participation with the principal investigator Hannover Medical School. This resulted in a final sample of 21 CTC-communities (16 small towns and five city districts) by July 2021.

Immediately after a CTC-community was recruited, individual 1:1-matching was used to identify comparable communities in the same federal state. For this, a nearest-neighbor matching procedure was applied to community-level data from official statistics 2017 (www.inkar.de) and police crime statistics (PCS) 2019, using indicators of municipality type, community development (growth vs. stable vs. shrinkage), long-term unemployment, fiscal power, criminality, vandalism, drug use as well as shoplifting rate in youth. For each recruited CTC-community, the comparison community with the best-matching score was requested to participate in the study. In case the community was not interested in participating, the next most similar community was contacted. Comparison communities were only eligible to participate in the study if (1) they had at least one secondary school, (2) they were not located in a county that implements CTC, (3) they were not directly adjacent to a CTC-community, and (5) they signed a cooperative agreement for study participation with the principal investigator Hannover Medical School. Overall, a sample of 21 matched pairs was recruited.

### Participants and eligibility

#### Community key informants

In each study community, people in leadership positions (e.g., mayors, city managers, police chiefs, school superintendents, business leaders, heads of social service agencies) will be invited to participate. These leaderships will be identified via the research staff and by using a snowball sampling method. Only those persons who have consented to the data collection will be interviewed.

#### Prevention actors

Prevention actors (directors of community agencies and coalitions, prevention program coordinators and staff, school principals, teachers) who are responsible for prevention activities and programs in the study communities will be invited to participate. These actors will be identified via the research staff and by using a snowball sampling method. Only those persons who have consented to the data collection will be interviewed.

#### Community board members

All members of the local CTC-prevention networks (community boards) will be invited to participate. Only those persons who have consented to the data collection will be interviewed.

#### CTC-trainers and local CTC-coordinators

CTC trainers and local CTC coordinators are invited to participate and to consent to the data collection.

#### Children and youth

Every secondary school in the study communities and relevant schools in the vicinity of these communities attended by a substantial number of community adolescents will be invited to participate. The survey will depened on the support of (1) school principals and (2) class teachers. Additionally, written informed consent of the (3) parents will be mandatory. Finally, (5) each student will have to consent to the survey. For the cohort survey, students of Grade 5 will be invited to participate. For the cross-sectional survey, students of Grades 6, 8, 10, 11 of secondary schools as well as students aged < 18 years of vocational schools are eligible.

### Measures

#### Effectiveness evaluation measures

##### Community key informant interviews (CKI)

A translated and adapted version of the CKI which was developed by Arthur, Glaser and Hawkins [33] will be conducted using computer-assisted telephone interviews. Data will be collected concerning (1) major changes or events in the community that could affect the local prevention activities; (2) the adoption of a science-based approach to prevention; (3) intersectoral collaboration for prevention; (5) community support for prevention; and (5) community norms against adolescent drug use.

##### Community resource documentation (CRD)

A translated and modified version of the instrument set [8, 22] will be used to measure the type, number, and scope of prevention activities. Using computer-assisted telephone interviews, data will be collected concerning the names of all evidence-based programs that were conducted in the community, how many participants each program has reached and the fidelity of this program. Program fidelity will include the subcategories program adaptation, adherence, dosage, participant responsiveness and oversight and will be based on previous items measuring program fidelity within CTC-contexts (see [22, 34, 35]). Additionally, cost data of the prevention activities and programs will be collected.

##### Children and youth survey (CYS)

A translated and adapted version of the US CTC survey [33], which was applied in Lower Saxony-wide surveys to establish reference values [36, 37], will be used to collect data on (1) socio-demographic variables (gender, age, parents living together, family size, language background, socio-economic status); (2) self-reported problem areas (violence, delinquency, substance use, truancy/temporary school drop-out, depressive symptoms, mobbing, intimate partner violence, discriminatory behavior, life and health satisfaction); (3) risk factors (community, family, school, peer/individual); (5) protective factors (community, family, school, peer/individual); (5) COVID-19 questions based on the JuCo study [38]. Each survey will take about 45 min and will take place during a school lesson as an online survey. For schools unable to provide an internet connection or computers, a paper version of the questionnaire will be available.

#### Process evaluation measures

##### Community board interview (CBI)

A translated and adapted version of the CBI will be used to monitor the implementation of CTC in the intervention communities. The CBI captures constructs associated with developing and maintaining an effective community coalition [39, 40]. The construct community coalition capacity captures five components [39]: (1) members’ substantive knowledge of prevention; (2) members’ acquisition of new skills; (3) members’ attitudes toward CTC; (4) organizational linkages to the coalition across community sectors; (5) and members’ perceptions of their coalition’s influence on organizations in the community on the development of intersectoral cooperation. The construct team functioning includes four components [40]: (1) goal directedness; (2) efficiency; (3) opportunities for participation; and (4) cohesion.

##### Milestones and benchmarks tool (MBT)

Additional measures of CTC implementation are obtained from ratings of the CTC Milestones and Benchmarks (see [41]). The CTC training materials describe “milestones” and “benchmarks” that are to be achieved during the five phases of CTC system implementation. The milestones are goals to be met by communities, and the benchmarks are the actions that community members take or conditions that must be present to achieve those goals. The local CTC-coordinators and the CTC-trainers are asked to send their ratings annually to the research team of this study.

### Outcomes

#### Primary outcomes

##### Primary short-term outcome

Based on the CYDS [21], we hypothesize that, compared to comparison communities, CTC-communities will (1) have stronger improvements regarding the adoption of a science-based approach to preventing youth problem behaviour, (2) have stronger improvements in intersectoral collaboration for prevention, and (3) have stronger improvements in community support for prevention.

##### Primary long-term outcomes

We hypothesize that CTC-communities will show lower prevalence and incidence of (1) antisocial behaviour and (2) substance use as well as (3) higher levels of well-being.

#### Secondary outcomes

##### Secondary short-term outcomes

Based on the CYDS [34], we hypothesize that, compared to comparison communities, CTC-communities will (1) implement more evidence-based prevention programs, (2) reach more persons with the implemented prevention programs, and (3) conduct the prevention programs with a higher fidelity.

##### Secondary long-term outcomes

We hypothesize that risk factors (community, family, school, peer/individual) which have been prioritized by the CTC-communities decrease whereas prioritized protective factors increase.

### Sample size calculation

For sample size calculations https://researchmethodsresources.nih.gov (Research Methods Resources: National Institutes of Health 2021) was used. Sample size calculations were conducted for the primary outcome in the short-term and long-term.

#### Primary short-term outcome: adoption score of science-based prevention

The calculation is for a net difference in a cohort study. We assume a type 1 error rate of 5%, desired power of 95%, correlation over time for the outcome variable of 0.6. A priori matching of the communities is considered with a correlation between matching factors and the outcome of 0.1 (individual level) and 0.2 (community level). Based on Brown et al. [21], regression adjustment for respondent characteristics is considered. An intraclass correlation coefficient (ICC) of 0.181 is assumed and for comparison communities a probability of 0.13 as well as for CTC-communities a probability of 0.34 of being in stage five of the adoption score (0–5) at post-test. Based on Muellmann et al. [42], 10 individuals (key informants) per cluster were considered. This results in a net sample size of 17 CTC-communities and 17 comparison communities with an average of 10 participants (key informants). Assuming a loss-to-follow-up of two matched pairs (four communities), a sample of 38 communities (19 matched pairs) and a total of 380 participants (key informants) is required.

#### Primary long-term outcomes: well-being, antisocial behavior, substance use

The sample sizes for the cohort and repeated cross-sectional design were calculated separately though largely relying on the same assumptions. Considering the heterogenous effects of the CYDS at the different follow-up intervals [43–45], we assume small effects (d = .2) for our primary outcomes in both the cohort and repeated cross-sectional design. We assumed a type 1 error rate of 5%, desired power of 80%, SD = 1, no adjustment for covariates, intraclass correlation of 0.013 [46]. An a priori matching of the communities (see below) was also considered with a correlation between matching factors and the outcome of 0.1 (individual level) and 0.3 (cluster level). For the cohort design, the calculation was based on a net difference assuming an average number of 150 individuals per cluster (community) and a correlation over time for the outcome variable of 0.7 (individual level) and 0.6 (cluster-level). For the cross-sectional design, the calculation was based on a simple difference assuming an average number of 450 individuals per cluster (community). Both calculations result in a required sample of 14 communities (7 per condition). The overall sample of students required for the cohort survey is *n* = 2100 and for the cross-sectional survey *n* = 6300. Assuming a loss-to-follow-up of two matched pairs (four communities), this results in a sample of 18 communities (9 matched pairs).

### Statistical methods

#### Effectiveness evaluation

##### Short-term outcomes

Changes in primary short-term outcomes (i.e., adoption of science-based prevention) will be assessed by using a three-level hierarchical linear model (HLM) [47] and a cumulative probability model [48] to model changes in each of the outcomes as a function of survey year (at Level 1) nested within respondents (at Level 2), in turn, nested within communities (at Level 3).

##### Long-term outcomes

Primary and secondary outcomes will be tested for differences between intervention and control by using either complex or multilevel structural equation models depending on the necessity to adjust for baseline differences between the student populations of the matched communities. Models will incorporate the nested data structure of students in classes/schools in communities in matched pairs. Additionally, baseline levels of the outcomes will be included in the cohort analysis. The primary analysis focuses on the effect of intervention group on the primary outcomes at the community level. As secondary analyses, hypothesized mediation and moderation paths and effects at school and individual level will be tested.

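### Long-term adjustment for differences between student populations hangs on an undefined necessity; in a self-selected design it should be fixed in advance, above all for the repeated cross-sections

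*Protocol article*

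**What the plan says.** Under Statistical methods, Long-term outcomes, the protocol article says that differences between the conditions will be tested with either complex or multilevel structural equation models, "depending on the necessity to adjust for baseline differences between the student populations of the matched communities". It does not say how necessity is judged, or which of the two models goes with adjustment.

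Two statements in the same paragraph carry no condition: "Models will incorporate the nested data structure of students in classes/schools in communities in matched pairs", and "Additionally, baseline levels of the outcomes will be included in the cohort analysis". The second is limited to the cohort. There is no matching sentence for the repeated cross-sectional surveys.

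On allocation, the section Assignment method and eligibility states: "The unit of assignment is the community, the assignment method is self-selection". It adds: "Individual 1:1-matching (see below) was employed to help minimize potential bias induced due to non-randomization". The matching indicators are community-level figures from official statistics of 2017 and police statistics of 2019. The section ends: "Overall, a sample of 21 matched pairs was recruited".

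The long-term sample size section treats the cohort as a net difference and the cross-sections as a simple difference, with "no adjustment for covariates" as an input.

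**The concern.** Where communities choose the intervention, the student populations may differ from the outset. Whether to adjust for that should not depend on whether a difference is noticed. With 21 communities per condition, a difference large enough to matter can easily look unremarkable.

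Matching does not settle the question, for three reasons:
- It used community statistics, not student data.
- The sample size section assumes a community-level correlation of only 0.3 between matching factors and outcome. That is 0.3² = 9% of the between-community variance, leaving 91% untouched.
- The surveyed students also pass through the agreement of principals, teachers, parents and the students themselves, and some attend schools outside the community. Composition can differ even between well-matched communities.

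At stake are residual confounding in the cases where adjustment is judged unnecessary, and a primary model that depends on a judgement which the reported interval does not reflect.

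**Working it through.** **1. The plan's own figure.** I took two-sided alpha 5% (sidedness is not stated), power 80%, d = 0.2, SD 1, ICC 0.013, and matching correlations of 0.1 (individual) and 0.3 (community). Quantiles are from t with 2(g−1) degrees of freedom, where g is communities per condition. At g = 7, (2.179 + 0.873)² = 9.31.

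- Cross-sections, simple difference, 450 students: g = 2[0.987 × 0.99/450 + 0.013 × 0.91] × 9.31/0.04 = 0.0280 × 9.31/0.04 = 6.5, rounded up to 7.
- Cohort, net difference, 150 students, correlations over time of 0.7 and 0.6: g = 4[0.987 × 0.99 × 0.3/150 + 0.013 × 0.91 × 0.4] × 9.31/0.04 = 0.0267 × 9.31/0.04 = 6.2, rounded up to 7.

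Both agree with the stated 7 per condition. At the 21 pairs recruited, the cross-sectional standard error is √(0.0280/21) = 0.037 and power for d = 0.2 exceeds 99%, adjusted or not.

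**2. What is conditional and what is not.**

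| Element | Cohort | Repeated cross-sections |
|---|---|---|
| Nesting and matched pairs | fixed | fixed |
| Baseline outcome | fixed | not promised |
| Other differences between student populations | conditional | conditional |

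**3. Illustration for the cross-sections.** From the protocol: ICC 0.013, 450 students per community, 21 communities per condition. Assumed, because the protocol gives none of them:
- adjustment is triggered when baseline community means differ at p<0.05;
- the true baseline difference δ is 0.05 to 0.10 SD;
- the community-level correlation over time is 0.6, which the protocol states for the cohort only.

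There is no CTC effect, and the comparison is of community means without pairing. With no adjustment, bias is 0.6δ. With adjustment for the observed baseline mean, a little bias remains because that mean is measured with error. Its reliability is 0.013/(0.013 + 0.987/450) = 0.856, so the remaining bias is 0.6 × (1 − 0.856) × δ = 0.087δ. The conditional rule was simulated (20,000 trials per row):

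| δ (SD) | Adjustment triggered | Bias: never / conditional / always (SD) | Type I error: never / conditional / always |
|---|---|---|---|
| 0.05 | 25% | 0.030 / 0.018 / 0.005 | 12.5% / 6.7% / 5.3% |
| 0.075 | 49% | 0.045 / 0.019 / 0.007 | 21.0% / 8.1% / 5.6% |
| 0.10 | 73% | 0.061 / 0.017 / 0.009 | 34.0% / 7.8% / 6.0% |

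Reducing the community variance by the matching factor 0.91 changes little: conditional bias is 0.016 to 0.018 SD and type I error 6.9 to 8.0%. With no true difference, the SD of the estimate is 0.037 under the conditional rule and 0.033 when always adjusting.

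**The case against.** The strongest reply is that the paragraph already protects the analysis: baseline outcome levels are unconditional in the cohort, and the matched pairs stay in every model. That stands. A reader might infer from the conditional clause that baseline adjustment of the whole long-term analysis is left open, and that precision is thrown away. The documents do not support this. The strongest single covariate is fixed in the cohort, and power is above 99% at 21 pairs in either design.

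Three other inferences also go too far:
- The article does not say that the complex model is unadjusted, only that the choice turns on the need to adjust.
- The phrase "no adjustment for covariates" is a sample size input, not an analysis rule.
- The type I errors of 12% and more belong to never adjusting, which the protocol does not propose.

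It is also fair that no test or threshold is stated, that necessity could be judged on substantive grounds, and that the size of imbalance is assumed. The figures above illustrate the rule and do not predict this trial. In the simulation baseline is the only confounder, which favours adjustment.

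Lastly, an article may leave criteria and covariate lists to the analysis plan. The missing list is therefore not the defect. The stated conditional rule is, and an analysis plan that follows it would inherit it.

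**Conclusion.** The point holds in a limited form. The protocol makes the long-term model, and with it adjustment for differences between student populations, depend on an undefined necessity in a design where assignment is by self-selection. This affects the repeated cross-sectional analysis, and student characteristics other than the outcome in both designs. It does not affect the baseline outcome in the cohort.

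Under the assumptions above, the size is modest. The largest conditional-rule bias, 0.019 SD, is about 10% of the planned effect (0.019/0.2), and type I error of 7 to 8% compares with 5 to 6% when always adjusting. Residual confounding is a risk and not a certainty: adjustment is made when judged necessary, and the matching is kept. Across the imbalances tried, the conditional rule gave more bias and a higher type I error than always adjusting.

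**What to change.** Delete the condition and prespecify one multilevel model per design, adjusted whatever the observed balance.

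- **Cohort:** keep the baseline outcome and add the socio-demographic variables already collected (gender, age, language background, socio-economic status).
- **Repeated cross-sections:** include the community-level mean of the outcome from the baseline survey wave and the same student variables. An individual baseline is not generally available here and should not be required.
- **Both:** retain the matched-pair structure. Do not enter all the matching indicators as separate community-level covariates, which 21 pairs cannot well afford. Report the unadjusted result as a sensitivity analysis.

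The change takes a few sentences in the analysis plan and needs no new data. The statistical price is one community-level degree of freedom for the baseline mean, and slight residual bias from measurement error in that mean (0.087δ in the illustration). The Discussion makes the long-term evaluation dependent on follow-up funding, so there should be time to fix the rule before it is used.

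### For the primary long-term outcomes, baseline outcome adjustment is fixed only for the cohort; the repeated cross-sections of self-selected communities are not committed to it, so residual pre-existing differences can be mistaken for a CTC effect.

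*Protocol article*

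**What the plan says.** All references are to the protocol article.

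- **Assignment method and eligibility:** "The unit of assignment is the community, the assignment method is self-selection". The safeguard is matching: "Individual 1:1-matching (see below) was employed to help minimize potential bias induced due to non-randomization". The matching variables come from 2017 official statistics and 2019 police statistics. They include municipality type, community development, long-term unemployment, fiscal power, criminality, vandalism, drug use and youth shoplifting.
- **Abstract, Methods:** "biennial cross-sectional surveys will be conducted in 6th, 8th, 10th, and 11th Grade in each community". The Design section adds that "data will be collected in a trend (repeated cross-sectional) and cohort design". Earlier community-level outcome data are therefore planned for both conditions.
- **Primary long-term outcomes (hypothesis):** "We hypothesize that CTC-communities will show lower prevalence and incidence of" antisocial behaviour and substance use, with higher well-being. This is a statement about level. The primary short-term hypotheses, by contrast, are about stronger improvement.
- **Sample size, long-term outcomes:** the cohort is sized on a net difference. For the other design, "For the cross-sectional design, the calculation was based on a simple difference". Both use no covariate adjustment.
- **Statistical methods, Long-term outcomes:** the model type for all long-term outcomes depends on whether adjustment for baseline differences between the student populations proves necessary. Then: "Additionally, baseline levels of the outcomes will be included in the cohort analysis".

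**The concern.** When communities assign themselves, a later difference in prevalence mixes any effect of CTC with whatever difference was there before. The plan handles this for the cohort by including the baseline outcome. For the cross-sections, three places lean towards a comparison of levels: the hypothesis, the simple-difference sizing, and the cohort-only sentence. The one remaining route to adjustment is conditional. It has no stated criterion, and it does not say whether the community's own earlier outcome level would enter.

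The consequence is that adjustment of a primary outcome in a non-randomised design could be decided after the data are seen, or not made at all, although the planned earlier waves supply what is needed.

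**Working it through.** **Inputs.** From the long-term sample size section: d = 0.2, SD = 1, ICC = 0.013, type 1 error 5% (taken as two-sided; the article does not say), power 80%, matching correlations 0.1 (individual) and 0.3 (cluster), 450 students per community for the cross-section, 150 for the cohort, and cohort over-time correlations 0.7 (individual) and 0.6 (cluster). From the eligibility section: 21 pairs.

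The credit for matching can be read in two ways, as factors (individual, cluster) of 1 − r² = (0.99, 0.91) or 1 − r = (0.9, 0.7). Both are carried through.

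**1. Reproducing the plan's figure of 7 per condition.** Write v for the variance per community, so that the standard error of the difference is √(2v/g) with g communities per condition.

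- Cross-section, simple difference: v = (0.987/450) × 0.99 + 0.013 × 0.91 = 0.01400.
- Cohort, net difference: v = 2 × [(0.987/150) × 0.99 × 0.3 + 0.013 × 0.91 × 0.4] = 0.01337.
- With t quantiles on 2(g − 1) df, both need g = 7 (power 0.828 and 0.844).
- With 1 − r and g − 1 df, v is 0.01107 and 0.01083, and both again need g = 7 (power 0.845 and 0.853).

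The stated size is correct. For the cross-section it reproduces as a one-wave comparison without baseline.

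**2. What matching leaves.** A cluster-level correlation of 0.3 explains 0.3² = 9% of between-community variance. The between-community SD is √0.013 = 0.114.

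**3. Size of the possible bias.** Suppose CTC has no effect and an average pre-existing difference of k community SDs persists; k is an assumption. With 21 pairs the standard error is √(2 × 0.01400/21) = 0.0365, or √(2 × 0.01107/21) = 0.0325 under the second reading. The rejection rate comes from the noncentral t with 20 df.

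| k | difference (d) | share of d = 0.2 | falsely significant |
|---|---|---|---|
| 0 | 0 | 0% | 5% |
| 0.25 | 0.029 | 14% | 12-13% |
| 0.5 | 0.057 | 29% | 32-39% |
| 1.0 | 0.114 | 57% | 84-92% |

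**4. Cost of adjustment.** Different students answer at each wave, so a cross-sectional net difference has v = 2 × [(0.987/450) × 0.99 + 0.013 × 0.91 × (1 − r_g)], where r_g is the cluster over-time correlation. The article gives 0.6 for the cohort only; using it here is an assumption, so a range is shown (1 − r² reading, 2(g − 1) df).

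| r_g | v | ratio to simple difference | g per condition |
|---|---|---|---|
| 0.6 | 0.01381 | 0.99 | 7 |
| 0.5 | 0.01617 | 1.16 | 8 |
| 0.3 | 0.02090 | 1.49 | 10 |
| 0 | 0.02800 | 2.00 | 13 |

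With 21 pairs, power at r_g = 0 is still about 0.96 (0.964 on 40 df, 0.955 on 20 df).

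Using the first-wave community mean as a covariate gives v × (1 − ρ²), where ρ is the correlation between the two wave means. This never exceeds the simple-difference variance. At r_g = 0.6, ρ = 0.013 × 0.91 × 0.6/0.01400 = 0.507 and v falls to 0.01040.

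**The case against.** A reader might infer that the plan analyses the cross-sections at post-test only and that pre-existing differences will be reported as a CTC effect. The documents do not support that. The term simple difference describes a sample size calculation, not the analysis. The design is called a trend design, which suggests comparison over time. The opening sentence on long-term methods covers all long-term outcomes and allows adjustment for baseline differences, and the cohort sentence begins as an addition to it. Individual baselines exist only in the cohort, so naming the cohort need not exclude community-level adjustment elsewhere. A condensed article may also leave model details to a fuller document.

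Matching is not empty either. Criminality, vandalism, drug use and youth shoplifting are related to two of the three primary outcomes. The imbalances in the bias table are assumed. A claim that adjustment costs no power would also go too far, since the variance of a net difference doubles at an over-time correlation of zero.

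All of this stands, and it limits the point to a risk. It does not remove the point. The article itself separates net from simple difference and fixes the baseline outcome for one design only. Its general provision has no criterion and speaks of student populations, without naming the community's earlier outcome level. Well-being has no direct counterpart among the matching variables. Making the adjustment firm is a better choice of method with data already planned, not a request for detail.

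**Conclusion.** The concern holds in this form: the plan does not commit the cross-sectional analysis of the primary long-term outcomes to the community's earlier outcome level, and self-selection with modest matching leaves room for bias. The sample size itself is not in error.

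The false-positive rates of 12-13%, 32-39% and 84-92% show sensitivity; they are not estimates. They assume a null effect, a persisting imbalance of 0.25, 0.5 or 1.0 community SD, two-sided testing, the plan's ICC of 0.013, and no adjustment being made.

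The first wave is also not a clean baseline, because CTC-communities entered in Phases 1 to 3. The article expects long-term outcomes to respond only after five years, so the wave remains useful, but adjustment should be described as reducing the bias.

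**What to change.** 1. In Statistical methods, Long-term outcomes, state with no data-dependent trigger that the cross-sectional model includes the community's first-wave level of the same outcome, by grade where available, as a community-level covariate. Alternatively, specify a condition-by-wave term with a community-by-wave random effect.
2. Word the primary long-term hypothesis to match, as a baseline-adjusted difference or a difference in change.
3. Align the sample size section. If the cross-section is restated as a net difference, give the assumed cluster over-time correlation and a range: 7 per condition at 0.6, and about 8, 10 and 13 at 0.5, 0.3 and 0.
4. Note that the first wave may not be fully pre-intervention in the CTC-communities.

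No new data are needed. The covariate costs about one degree of freedom. A net difference loses some precision if the over-time correlation is low, but every case shown stays within the 21 recruited pairs.
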